### Sample size

Power calculation is based on current standards in neuroimaging. For (f)MRI, the recommended number of subjects for between-group designs is 20 (Thirion et al., [92]). In addition, from previous studies we know that groups of 20 subjects per condition are sufficient to detect significant differences in (neuro) physiological parameters measured with fMRI [17, 18]. Similarly, a group of 22 subjects were sufficient to detect significant treatment effects measured with MRI [13]. Based on previous work at the ECCF (Knoop et al., [5]) it is assumed that approximately 50 % of the CFS patients in the CBT condition will show significant improvement (for definition: see above). Accordingly, to be able to compare successfully treated patients with non-successfully treated patients we will include twice as many patients in the CBT condition as in the waiting list condition. Assuming that 10 % of the measurements (from baseline as well as 2nd assessment) will yield technically insufficient data, 17 % of the patients will drop out from the study and a ratio of 2:1 (CBT: waiting list), we will include 30 healthy controls, 30 patients in the waiting list condition and 60 patients in the CBT condition (Fig. 3). Based on previous clinical work (Knoop et al., [74]; Wiborg et al., [9]), we expect a mean decline of–15.2 (±15.8) for patients in the CBT condition and–5.2 (±7.2) for patients in the waiting list condition. Accordingly, assuming an alfa of 0.05 and a power of 0.95 this will also yield enough power to replicate previous reported treatment effects on the primary clinical outcome measures. Note that technical failure of MRI measurements will not affect the collection of clinical measures.

**Fig. 3 Fig3:**
[figure not shown]
Flowchart of inclusion. CFS = Chronic fatigue syndrome, CBT = Cognitive behavioural therapy

### Randomization

CFS patients will be randomized to either the CBT condition (66 %) or waiting list condition (33 %). Randomization will take place per patient after the first session day in the presence of the therapist and patient, either during the second diagnostic appointment with the therapist or during a phone call with the therapist. Randomization will be done by supporting staff of the ECCF who are not directly involved in the study. Concealed allocation will be guaranteed by using a central web-based randomization program, developed by an independent statistical advisor. Patients randomized to the intervention group will start treatment directly and will be treated with CBT for CFS (see above). Patients randomized to the control group will start with CBT for CFS 6 months later, after the second assessment. The researchers that will collect and analyze the data are not blind to the allocation, because knowledge of treatment progress is necessary for the planning of the second test day.

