## Methods/design

### Study design

A RCT will be conducted to investigate neural correlates of change brought on by CBT in patients diagnosed with CFS. CFS patients will be randomly assigned to either the intervention group (N = 60), which will immediately start with CBT, or the waiting group (N = 30), which will start with CBT after a 6 months waiting period. In order to compare CFS patients that recover from CBT with those that do not we will use a 2:1 allocation ratio for CBT and waiting group respectively. MRI measurements, behavioral measures, questionnaires and biomarker sampling will be gathered at baseline and at a second session after approximately 6 months in both groups. Results will be compared to 30 age, gender and education matched healthy controls, which will also be tested twice, separated by a 6 months period (Fig. 1).

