### Intervention

CBT for CFS (Heins et al., [67]; Wiborg et al., [9]) aims at recovery, meaning that the CFS patient is no longer severely fatigued and disabled by the fatigue, by changing cognitions and behaviors assumed to perpetuate the symptoms. Previous trials have repeatedly demonstrated that CBT for CFS leads to a significant reduction of fatigue and disability ([68]; Prins et al., [69]; White et al., [6]; White et al., [70]; Wiborg et al., [9]) and to recovery in a subset of patients (Knoop et al., [5]; White et al., [6]). CBT treatment will be given by trained cognitive behavioral therapists at the ECCF of the radboudUMC in Nijmegen, the Netherlands. Treatment consists of 12–14 individual sessions with a trained cognitive behavioral therapist within a period of approximately 6 months. The treatment starts with explanation of the cognitive behavioral model of CFS and goal setting. Patients formulate their goals in concrete activities they will do when they are no longer bothered by fatigue, e.g. resumption of work or study. Then, patients will learn to regulate their sleep-wake cycle by maintaining fixed bedtimes and no longer sleep or lie down during the day. Once the sleep-wake cycle is regulated, patients will start with a graded activity program consisting of a graded increase in walking of cycling activities. Based on their physical activity patterns, relative active patients will first learn to better divide activities across the day before starting with the graded activity program and low active patients will start directly with the graded activity program. Dysfunctional fatigue-related cognitions, e.g. catastrophising in response to fatigue, low self-efficacy and increased focus on symptoms are challenged continuously throughout the intervention. When activity levels are increased and patients attain the belief that they have potential to be more active, they start with realization of their prior set goals. The last part of the intervention aims at reappraisal of fatigue as a normal sensation and prevention of relapse.

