### Session procedure

Participants will be invited to the Donders institute for brain cognition and behavior on two session days separated by approximately 6 months. Each session will include the following procedures: (1) hair and blood sampling. (2) practice of fMRI tasks, including the calibration of MVC for the two fMRI tasks. The practice session is done in a dummy scanner to ensure same body position during handgrip-calibration, practice and fMRI-scanning. (3) MRI scanning, including six scans and a 15 minute break: structural MRI, fMRI during task1, MRS, break, fMRI during task2, DTI and resting state. (4) Behavioral and neuropsychological testing. The order is kept the same across subjects and sessions. An overview of a session day is given in Fig. 2. Written informed consent is given on the first session day. Trait measures such as the adult reading test are only assessed on the first test day. POMS measurements are assessed before sampling, during the break and after behavioral testing. The total duration of each session will be about 5 hours. For CFS patients, questionnaires are assessed as part of the clinical routine of the ECCF prior to the session days. For healthy controls, questionnaires are assessed at home through an internet link, sent to the subjects by email.

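### The need to plan the second test day does not justify leaving image processing, quality exclusions and analysis unmasked

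*Protocol article*

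**What the plan says.** The Randomization section of the protocol article says: "The researchers that will collect and analyze the data are not blind to the allocation, because knowledge of treatment progress is necessary". The need it names is the planning of session 2, and no other reason is given. The same section assigns randomization to supporting staff of the treatment centre who have no direct part in the study, and it takes place after the first session day.

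The Analysis section lists a baseline comparison with healthy controls, a comparison of change between CBT and waiting list, and a comparison of change between improved and non-improved patients within the CBT condition. The Sample size section assumes that 10% of "measurements (from baseline as well as 2nd assessment) will yield technically insufficient data" and that 17% of patients drop out.

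On timing, Study design places the measurements "at baseline and at a second session after approximately 6 months in both groups", and Session procedure has all participants attend "on two session days separated by approximately 6 months". The Intervention section says: "Treatment consists of 12–14 individual sessions with a trained cognitive behavioral therapist within a period of approximately 6 months". For the waiting list, the Randomization section says: "Patients randomized to the control group will start with CBT for CFS 6 months later, after the second assessment".

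**The concern.** The reason given is narrower than the decision it supports. Someone has to know how far a patient is in treatment in order to book session 2. That does not require the person who fits a spectrum, preprocesses a scan, rejects a measurement or specifies a model to know the arm.

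The trial's stated purpose is to explore neural mechanisms, and those outcomes pass through many discretionary steps between scanner and test statistic. If the steps are taken with the arm known, expectations about CBT can enter the between-arm contrast. Knowledge of treatment progress may also hint at who is responding, which exposes the responder comparison in the same way.

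A second, weaker question follows from the same sentence. Treatment progress informs the date of session 2, but waiting-list patients have no treatment progress before that session. The rule for dating session 2 may therefore differ between arms. The Background says the patient control group is there to separate treatment from time, so the interval matters.

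**Working it through.** **Does the reason cover the decision?**

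- Task that needs treatment progress: planning the second test day (Randomization).
- People left unblinded: those who collect and those who analyze (Randomization).
- People who could book without analyzing: the therapist, who is present when the patient is randomized, and the support staff who perform randomization (Randomization).

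Nothing in the article links processing or analysis to booking. The stated reason does not reach them.

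**Which outcomes are exposed?**

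- CIS fatigue and SIP8: questionnaires completed by patients in clinical routine (Outcome measures; Session procedure). Masking analysts does not protect how they are answered.
- Baseline collection: done before randomization, so the operator cannot know the arm.
- Imaging, spectroscopy, task and assay data at processing and analysis: exposed.
- Session 2 collection: exposed, and only partly protectable, because patients know their arm and may say so.

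**The plan's own numbers.** Inputs from Sample size: target 20 per imaging group (40 for CBT, at twice the waiting list), dropout 17%, technical failure 10% at each session.

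- Waiting list: 20 / (0.83 × 0.90 × 0.90) = 29.7, so 30.
- CBT: 40 / (0.83 × 0.90 × 0.90) = 59.5, so 60.

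Both match the planned sizes. In the other direction, 60 × 0.83 × 0.81 = 40.3 and 30 × 0.83 × 0.81 = 20.2, so about 40 versus 20 are evaluable.

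**Detectable difference at 40 versus 20.** SE = √(1/40 + 1/20) = 0.274 SD. The normal approximation at two-sided 0.05 and 80% power gives (1.960 + 0.842) × 0.274 = 0.77 SD; the t distribution with 58 degrees of freedom gives 0.78 SD. The 80% power and the two-sided test are assumptions made here. The article states power only for the clinical outcome (0.95) and does not state sidedness.

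**Worst-case shift from selective exclusion.** Assume normal outcomes and that the discarded 10% are exactly the lowest values in one arm. The retained mean moves by φ(−1.2816) / 0.90 = 0.1755 / 0.90 = 0.195 SD. If the other arm loses exactly its highest 10%, the contrast moves by 2 × 0.195 = 0.39 SD. As shares of the detectable difference:

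- 0.195 / 0.78 = 0.25
- 0.39 / 0.78 = 0.50

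If failures are unrelated to outcome, the shift is 0.

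**Effect on the 5% error.** With no true effect and a bias of b SD, the two-sided error is 1 − Φ(1.96 − b/0.274) + Φ(−1.96 − b/0.274). The values of b are assumptions:

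| b (SD) | error at 40 v 20 |
|---|---|
| 0 | 5% |
| 0.1 | 6.5% |
| 0.2 | 11% |
| 0.3 | 20% |

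**Timing.** Both arms have the same nominal interval of about 6 months, with no window stated. CBT itself is also put at about 6 months, in 12–14 sessions. Treatment progress feeds into the date in one arm and has no counterpart in the other. That is a possible difference in scheduling rule. No difference in mean or spread of interval can be computed from the text.

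**The case against.** Several points on the other side are fair.

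- The 0.195 and 0.39 SD figures require exclusions chosen entirely by outcome and, for the larger, in opposite directions. The 10% is an expected technical failure rate, not a pool of discretionary rejections. This stands: the figures are ceilings and the floor is zero.
- The article does not say who judges data quality, when, or by what rule. A condensed article may leave quality thresholds and pipeline details to a fuller document. This stands too, so their absence is not the criticism. The criticism is of what the article does fix, namely that those who collect and analyze know the allocation.
- Some protection exists: spectroscopy voxel size and targets are set in advance, session order is constant, and baseline collection precedes randomization. These limit the exposure but do not reach later processing and analysis.
- Patients and therapists cannot be blinded, so full blinding is out of reach. Agreed; masked processing and analysis does not depend on it.

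A reader might also infer that the interval between scans actually differs by arm and so confounds CBT with elapsed time. The documents do not support that. Study design and Session procedure give both arms the same nominal interval, and treatment progress may do no more than adjust the day within it.

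**Conclusion.** The point stands for processing and analysis. The article affirmatively leaves analysts unblinded, and its only reason concerns booking. The conclusion covers imaging, spectroscopy, task and assay outcomes. It does not cover CIS fatigue, SIP8 or baseline collection.

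The size of the bias is unknown. Fully outcome-selective exclusion of 10% bounds the shift at 0.195 SD (one arm) or 0.39 SD (both arms, opposite directions), which is a quarter to a half of the difference detectable at 40 versus 20. These bounds assume normal outcomes and 10% discarded per arm. They are not predictions.

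The timing point is secondary and an inference: treatment progress can inform the session 2 date in one arm only, but no difference in interval is shown. Neither point invalidates the trial. The masking should be put right before data are processed, because exclusion decisions taken with the arm known cannot later be made blind by the same people.

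**What to change.** 1. Have the therapist, or the support staff who already randomize, book session 2.
2. Release images, spectra, task files and assay results to those who process and analyze them under codes carrying neither arm nor responder status.
3. Lock quality exclusions and preprocessing before the codes are opened.
4. Replace the sentence in Randomization with one saying who knows the allocation and who does not, and that session 2 operators may learn it from patients.
5. State one scheduling window around the nominal 6 months for both patient arms, and report the actual interval by arm. Do not adjust for the interval as a covariate: if treatment progress influences it, it is a post-randomization variable and adjustment can introduce bias. Do not match waiting-list intervals to CBT intervals either, since CBT for those patients follows their second assessment and matching could delay it.

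The cost is minor logistics: file recoding and booking by existing staff. Sample size and power are unchanged, because none of their inputs is touched. Two limits remain. Session 2 operators may still learn the arm, and under a common window some CBT patients may be scanned before their last session, which the interval report should make visible.

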## Discussion

This study will investigate neural mechanisms underlying CFS symptoms and its changes after CBT. The aims are threefold. First, we will replicate and extend previously found anatomical findings, second, we will explore underlying neural mechanisms using functional neuroimaging and third, we will collect biomarker measures from blood, hair and saliva to assess cytokine and cortisol changes during CBT.

To our knowledge, this will be the first randomised controlled trial investigating neural mechanisms of change brought on by CBT for CFS. There are a limited number of studies that investigated neural changes after CBT in CFS [14] or CBT in other disorders (Seminowicz et al., [93]). However, those studies often relied on small samples (<20) and seldom used a no-treatment patient control condition. Here we overcome those problems by collecting data of more patients and by including a waiting list control condition. Because we will include twice as many patients in the CBT condition as in the waiting list condition, this study will allow us not only to investigate changes between CBT and waiting list conditions, but also to investigate changes within the CBT group between those patients that benefit from CBT and those that do not. This creates a unique change to investigate the neural mechanisms of change of CBT and to identify biomarkers that may predict treatment outcome.

We aim to replicated previously found anatomical findings [13, 14] and extend these findings with additional anatomical information using MRS and DTI. With respect to functional neuroimaging and behavioral assessment, task selection and hypotheses are based on a combination of clinical observations, cognitive behavioral models of CBT and a recent neurobiologically informed Bayesian model of medically unexplained symptoms. This translation between clinical observations and fundamental neuroscience models is unique in the investigation of CFS and an important step forward in understanding the etiology of CFS symptoms and the mechanisms of change of CBT.

Taken together, this project creates a unique opportunity to enhance our understanding of CFS symptoms and its change by CBT in terms of neuroanatomical, neurofunctional, behavioural, immunological and endocrinological mechanisms. Moreover, the comparison of patients that benefit from CBT with those that do not may lead to new insights for treatment resistant CFS patients.
